## Abstract

**Background::**

Allergic rhinitis is a global problem. About 10% to 40% of the global population is affected by allergic rhinitis and is on the rise, which has a significant health and economic impact on society. Ear acupuncture is a non-invasive acupuncture therapy, which has been used in the treatment of allergic rhinitis, and some positive results have been reported, but there is not enough evidence to prove its efficacy and safety.

**Methods::**

This is a single-center, randomized, single-blind, sham-controlled trial. With the approval of the ethics committee of our hospital, participants with allergic rhinitis will be randomly assigned to receive either real or sham ear acupuncture once a week for 8 weeks, followed by 12 weeks of follow-up. Evaluate the patient's nasal symptom score and Standardised Rhinoconjunctivitis Quality of Life Questionnaire score, and monitor adverse events. Finally, the data are analyzed by SPSS 22.0 software.

**Discussion::**

The results of this study will determine the efficacy and safety of ear acupuncture in the treatment of allergic rhinitis and provide a basis for promoting the application of ear acupuncture in the treatment of allergic rhinitis.

**Trial registration::**

OSF Registration number: DOI 10.17605/OSF.IO/MVEF7.

## Introduction

1

Allergic rhinitis (AR), also known as nasal allergy, is a non-infectious inflammatory disease of the nasal mucosa. It occurs after exposure to allergens, is mediated by IgE antibody and involves various immune cells and cytokines. Allergic rhinitis is a global problem, with the prevalence rate for adults and children being 14% and 13%, respectively, in the United States,^[1]^ It affects about 10% to 40% of the global population.^[2]^ It is known to interfere with sleep, attention, memory, quality of life, work, study,^[2–4]^ and driving ability posing a threat to traffic safety.^[5]^ In addition, AR is believed to be a risk factor for asthma, sinusitis, and other comorbidities.^[2,6]^ Current treatments for allergic rhinitis include minimizing exposure to allergens, the use of drugs to alleviate symptoms, anti-inflammatory therapy, and allergy immunotherapy (AIT).^[3]^ However, in clinical practice, it is difficult for many patients to control their symptoms effectively, whether they are treated with a single drug or a multi-drug combination of drugs,^[7]^ at the same time, there are some side effects,^[8]^ so there is an urgent need to find new alternatives.

In China, acupuncture is widely used in various diseases. It has the functions of regulating immunity and anti-inflammation through specific acupuncture point stimulation,^[9]^ and its efficacy has also been recognized by medical science in the world, becoming a new drug replacement therapy.^[10]^ Ear acupuncture (EAP) is a noninvasive semi–self-administered form of acupuncture. As a kind of acupuncture, auricular points have a long history in China. By stimulating specific acupoints on the ear in a non-invasive way, it has the functions of regulating endocrine, improving immunity and anti-allergy and so on. It is widely used in insomnia, obesity, acute and chronic pain, and other diseases.^[11–15]^ Previous studies have shown that EAP is also effective and safe for AR.^[16]^ But there is not enough evidence to prove this. Therefore, we plan to conduct a randomized, controlled, prospective clinical study to observe the efficacy and safety of EAP in the treatment of allergic rhinitis, so as to provide a basis for promoting the application of EAP in the treatment of allergic rhinitis.

## Method

2

### Study design

2.1

This study is a single-center, single-blind, randomized, and controlled clinical study. This study protocol has been approved by the Ethics Committee of our hospital and fully complies with the Helsinki Declaration in the process of implementation. The design, implementation, and results report of this scheme will be carried out in accordance with the requirements of SPIRIT 2013 Statement^[17]^ and CONSORT 2010 Statement.^[18]^ This research program has been registered in the open science framework (OSF) (registration number: DOI 10.17605/OSF.IO/MVEF7). The study flow chart is shown in Figure 1.

**Figure 1 F1:**
[figure not shown]
Flow diagram.

### Patient population

2.2

#### Participants source and sample size estimation

2.2.1

We will include patients through pre-hospital recruitment and screening of inpatients. After qualification assessment, patients will be informed of the protocol and purpose of the trial, and will be included in the study only after consenting to the study and signing an informed consent form.

Sample size estimation will be based on post-treatment Total nasal symptom score.^[19]^ According to the pre-experiment results, the real EAP group was 2.82 ± 1.48, and the Sham EAP group was 3.47 ± 1.57, α = 0.05, β = 0.2, and 107 samples were needed in each group according to the calculation by PASS15.0 software. Consider a drop-out rate of no more than 20%, with 134 cases in each group.

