### Statistical analysis

2.8

The data were analyzed by SPSS.22 software package, the hypothesis test was two-tailed test, and the α level was set to *P* < .05. The measurement data in accordance with normal distribution and homogeneity of variance are tested by independent sample *T* test, while those inconformable are tested by Mann–Whitney *U* test.

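### The stated means, SDs, alpha and beta require 88 evaluable patients per group, not 107, so the sample size and its 80% power do not reconcile

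*Protocol article*

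**What the plan says.** Section 2.2.1 (Participants source and sample size estimation) gives one self-contained calculation. The endpoint is named: "Sample size estimation will be based on post-treatment Total nasal symptom score". The pilot results are that "the real EAP group was 2.82 ± 1.48, and the Sham EAP group was 3.47 ± 1.57", and the error rates are "α = 0.05, β = 0.2". From these the section concludes that "107 samples were needed in each group according to the calculation by PASS15.0 software". It then allows for attrition: "Consider a drop-out rate of no more than 20%, with 134 cases in each group".

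Section 2.8 (Statistical analysis) settles the sidedness, "the hypothesis test was two-tailed test", and names the independent-sample t test, with Mann–Whitney U where normality or equal variance fails. The article states no unequal allocation, multiplicity adjustment, non-parametric allowance, or other SD or difference for the calculation.

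**The concern.** A sample size for comparing two means needs a difference, the SDs, alpha, power, sidedness and the allocation ratio. The article supplies all of these and presents 107 as their consequence, so the figure should reproduce. It does not, and the gap is too large for rounding or choice of formula.

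Section 2.2.1 is the only justification the article gives for the size of the trial. If the printed inputs are right, the declared 80% power is wrong for the planned size, or the trial will randomise patients whom its own assumptions do not require. If 107 is right, one of the published inputs is wrong, and readers will judge the result against the wrong assumed effect or variability.

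**Working it through.** **Inputs.** From section 2.2.1: means 2.82 and 3.47, so the difference is 0.65; SDs 1.48 and 1.57; α = 0.05; power 1 − 0.2 = 0.80; equal groups; drop-out 20%. From section 2.8: two-sided test, t test as first choice.

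**The plan's own drop-out step.** 107 / (1 − 0.20) = 133.75, rounded up to 134. This reproduces, so the fault lies in the step from the inputs to 107.

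**Normal approximation.**

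n per group = (z₀.₉₇₅ + z₀.₈₀)² × (SD₁² + SD₂²) / difference²

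= (1.960 + 0.8416)² × (1.48² + 1.57²) / 0.65²

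= 7.849 × 4.6553 / 0.4225 = 86.5, so **87 per group**.

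**Noncentral t.** The pooled SD is √(4.6553 / 2) = 1.526 and the standardised effect 0.65 / 1.526 = 0.426. The noncentrality is 0.426 × √(n/2) with 2n − 2 degrees of freedom.

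| Evaluable per group | Power for 0.65 |
|---|---|
| 87 | 0.798 |
| 88 | 0.802 |
| 107 | 0.873 |
| 134 | 0.935 |

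The smallest size reaching 80% is **88 per group**. Welch's test with the two separate SDs also gives 88. After drop-out, 88 / 0.80 = 110 per group.

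**Gap.** 107 − 88 = 19 evaluable per group (19/88 = +22%). Randomised: 134 − 110 = 24 per group, or 268 − 220 = 48 in total.

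**What 107 per group corresponds to at 80% power (t test).** A difference of about 0.59 with the printed SDs, or a common SD of about 1.69 with the printed difference.

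**Other readings tried** (two-sided α = 0.05 and 80% power unless noted):

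| Variation | n per group |
|---|---|
| Means and SDs moved to the limits of their rounding | 85 to 91 |
| SD 1.48 in both arms | 83 |
| SD 1.57 in both arms | 93 |
| Mann–Whitney, normal data (88 × π/3 = 92.2) | 93 |
| Mann–Whitney, worst-case efficiency (88 / 0.864 = 101.9) | 102 |
| One-sided α = 0.05 | 69 |
| 90% power | 117 |
| Two-sided α = 0.025 | 106 |
| 85% power, SD 1.57 in both arms | 106 |
| SD 1.57 in both arms plus a 15% allowance (93 × 1.15 = 106.95) | 107 |

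The last three rows come close to 107 or reach it. The first of them contradicts the stated alpha, the second contradicts the stated beta, and the third needs a common SD and a 15% allowance that section 2.2.1 does not mention. Also, 88 × 1.2 = 105.6, rounded up to 106, so drop-out may have been applied twice; that is conjecture.

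**The case against.** The best counter-argument is that 107 may be a correct PASS output from inputs the article did not print. Section 2.8 names Mann–Whitney U as the fallback. Taking the larger SD in both arms gives 93, and a 15% non-parametric allowance then gives 107; dividing 93 by the worst-case efficiency of 0.864 gives 107.6. On that account neither the power nor the size need be wrong, and calling 48 patients surplus presumes that the printed inputs are the true ones.

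This is fair as far as it goes. It shows that an undisclosed input could account for the number, and it means the error cannot be pinned on the sample size alone. It does not make the paragraph reproduce: an SD is printed for each arm, and no allowance is mentioned.

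A second objection is that the error is conservative. That also stands, on the printed inputs: the primary comparison is not underpowered, and no estimate, test or type I error rate is affected. It limits the harm but does not make the power statement correct.

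Nor does the condensed format of an article explain the gap. Nothing here has been left to a fuller document; inputs and result are printed together and disagree.

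**Conclusion.** The concern holds. On the stated inputs, with a two-sided t test and equal groups, the requirement is 88 evaluable and 110 randomised per group, against 107 and 134 in the article. At 107 evaluable per group the power is 87.3%, not 80%.

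The conclusion assumes that the printed means, SDs, alpha and beta are the ones intended. If one of them is misreported, 107 may be right and the pilot figures or error rates wrong. In either case section 2.2.1 cannot stand as written. Confidence in the arithmetic is high: the normal approximation, the noncentral t and Welch's test agree to within one patient per group.

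**What to change.** Retrieve the PASS procedure and every input entered (test, SDs, difference, alpha, sidedness, power, any non-parametric allowance), then correct section 2.2.1 according to what is found:

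1. **A different input was used.** State it, so that 107 reproduces. The 134 then follows without change.
2. **The printed inputs are correct and the size is kept.** Keep 134 randomised per group and state that 107 evaluable per group gives about 87% power for a difference of 0.65, or 80% power for about 0.59.
3. **The printed inputs are correct and 80% power is kept.** State 88 evaluable and 110 randomised per group.

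The third option should not be taken before the inputs are traced. If the true common SD were 1.69, for example, 88 per group would give a noncentrality of (0.65 / 1.69) × √44 = 2.55 on 174 degrees of freedom, and power of only about 72%.

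The cost is the rewording of one paragraph. No option adds patients.

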### Outcome measures

2.5

The main outcome indicator is the decrease of Total nasal symptom score^[19]^ (including self-assessment in several aspects of nasal congestion, runny nose, nasal itching, sneezing, difficult sleep). The secondary outcome indicators are Standardized Rhinoconjunctivitis Quality of Life Questionnaire (RQLQ)^[21]^ and mitigate changes in drug use. Data were recorded by Case Report Forms (CRFs) during treatment (8 weeks, weekly) and follow-up (12 weeks, every 3 weeks). Considering the possibility of pellets falling off during treatment, participants were asked to record how many pellets were still attached to their auricular points in the CRFs every day. The total number of pellets remaining each week was analyzed as treatment dose data.

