### Adverse events and termination of trial

2.6

For safety reasons, we will record all unexpected reactions related to the study treatment with detailed description, including time of occurrence, duration of symptoms, severity of symptoms, management measures, time when adverse reactions disappear and classification of causality. The investigator will document and manage all adverse events, whether or not they are related to the study treatment. If more than 25% of patients stop the intervention due to adverse events, the superior physician will make the decision to terminate the trial. The case report form (CRFs) will be used for data collection to record demographics, assessments, and reasons for patient withdrawal. At the end of the study, the investigators will submit the CRFs form to the data Management Committee.

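### The only named analysis, a two-sample test, makes no use of intermediate scores or of baseline as a covariate; a baseline-adjusted repeated-measures model would be more precise and less exposed to response-related drop-out

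*Protocol article*

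**What the plan says.** - **Section 2.2.1 (sample size).** The inputs are post-treatment Total nasal symptom scores (TNSS): "the real EAP group was 2.82 ± 1.48, and the Sham EAP group was 3.47 ± 1.57". The requirement is "α = 0.05, β = 0.2, and 107 samples were needed in each group", and then "Consider a drop-out rate of no more than 20%, with 134 cases in each group".
- **Section 2.5 (outcomes).** "The main outcome indicator is the decrease of Total nasal symptom score". On timing: "Data were recorded by Case Report Forms (CRFs) during treatment (8 weeks, weekly) and follow-up (12 weeks, every 3 weeks"). I read the recorded data as including TNSS; a decrease also presupposes a baseline score.
- **Section 2.6.** The case report forms also serve "to record demographics, assessments, and reasons for patient withdrawal".
- **Section 2.8 (analysis).** "the hypothesis test was two-tailed test", at the 0.05 level. "The measurement data in accordance with normal distribution and homogeneity of variance are tested by independent sample" t test, and otherwise by the Mann-Whitney U test. No other analysis is named.

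The article gives no analysis set, no rule for missing scores and no visit for the primary comparison.

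**The concern.** A two-sample test compares one number per participant. Applied to one visit, it leaves out anyone without that visit's score unless a value is imputed. The scores that a participant gave before leaving then contribute nothing. Even for those who stay, the intermediate weeks are unused, and baseline enters at most through subtraction.

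Two things are at stake. The first is precision: an unadjusted comparison has a wider confidence interval than the same data could give. The second is bias: if participants with poor scores leave one arm more readily than the other, those who remain are no longer the randomised groups. Raising enrolment from 107 to 134 per group restores the number analysed but does not remove such bias.

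Arm-dependent loss cannot be excluded. The outcome is self-assessed, participants press the pellets three times a day for 8 weeks, and the acupuncturist knows the allocation.

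**Working it through.** **1. The plan's own drop-out step.** 107 / (1 - 0.20) = 133.75, rounded up to 134. This reproduces. (The 107 itself does not follow from the stated inputs. The difference is 3.47 - 2.82 = 0.65 and the pooled SD is 1.526, so n = 2 × 1.526² × (1.960 + 0.842)² / 0.65² = 86.5, that is 87 per group, or 88 by the exact t calculation. With 107 the power is about 87%. That is a separate matter and errs on the safe side.)

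**2. Precision, by formula.** Assume SD 1.53 at both times, baseline-to-week-8 correlation ρ = 0.6 (not in the article) and 107 analysed per group, so √(2/107) = 0.1367.
- Raw week-8 score: 1.53 × 0.1367 = 0.209.
- Decrease: SD = 1.53 × √(2 × (1 - 0.6)) = 1.368; SE = 1.368 × 0.1367 = 0.187.
- Week 8 adjusted for baseline: SD = 1.53 × √(1 - 0.6²) = 1.224; SE = 1.224 × 0.1367 = 0.167.

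The ratio of the last two is √(2/(1 + ρ)): 1.12 at ρ = 0.6, rising to 1.41 at ρ = 0 and falling to 1 as ρ approaches 1. Under three assumed correlation patterns, simulation gave an SE of about 0.17 for the repeated-measures estimate against 0.19 for the t test on the decrease, 0.18 against 0.22, and 0.21 against 0.27. Across all runs the ranges were 0.17 to 0.21 and 0.18 to 0.28. Most of the gain at ρ = 0.6 is already in the 0.167, so it comes from baseline adjustment rather than from the intermediate weeks.

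**3. Bias on the raw post-treatment score.** Large-sample simulation with assumed inputs: eight weekly scores, SDs as in 2.2.1, correlation between adjacent weeks of 0.70 / 0.85 / 0.95 decaying with distance, about 20% drop-out, and odds of leaving × 2.7 per 1.5 points of worse last score where drop-out is score-driven. The true difference is 0.65 (sham minus real).

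| Drop-out | Difference in those remaining | Power | Estimate using all weekly scores |
|---|---|---|---|
| Unrelated to score | 0.657 / 0.644 / 0.651 | 0.885 / 0.870 / 0.876 | 0.658 / 0.644 / 0.651 |
| Same rule, both arms | 0.614 / 0.593 / 0.585 | 0.847 / 0.831 / 0.840 | 0.652 / 0.650 / 0.662 |
| Score-driven, sham only | 0.548 / 0.470 / 0.387 | 0.753 / 0.628 / 0.482 | 0.652 / 0.649 / 0.648 |
| Score-driven, real only | 0.736 / 0.801 / 0.880 | 0.943 / 0.973 / 0.991 | 0.652 / 0.647 / 0.651 |

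Subtracting 0.65, the bias is -0.036 to -0.065 with the same rule in both arms, -0.10 to -0.26 with sham only, and +0.09 to +0.23 with real only. With no true effect, the rejection rates were 0.050 to 0.054, 0.086 to 0.250 and 0.069 to 0.207 respectively. A second set of runs (134 per arm, SD 1.53, score-driven loss in sham only) gave about -0.16 to -0.23 across its assumed correlations. Its case with equal correlation 0.6 between all visits had drop-out of 23.5% in sham and 17.1% in real, bias of about -0.22, rejection of about 18 to 20% under no effect, and power of about 56%.

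**4. Bias on the stated outcome, the decrease.** In that last case, the same drop-out with the t test applied to the decrease gave bias +0.02 and 4.6% rejection under no effect. Under the alternative it gave 0.675 (bias 0.675 - 0.65 = +0.025) and power 94.5%. Across the assumed correlations the bias was +0.01 to +0.05 and rejection about 5%. The reason is simple: those who stay in sham have lower week-8 scores and also lower baseline scores, and the subtraction removes most of the shift.

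**The case against.** The strongest reply is that section 2.8 is two sentences in a condensed article. A reader might infer that only completers will be analysed and that the weekly scores are to be thrown away. The documents say neither. A t test is compatible with all randomised participants and imputed scores, and dividing by 0.80 is routine arithmetic that does not define an analysis population. Analysis sets and missing-data rules are often left to a fuller protocol or an SAP, so their absence here is not an error. All of this stands.

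A reader might also infer from the raw-score simulations that a third of the effect could vanish, or that the false-positive rate approaches 18%. That does not carry over to the stated outcome. It further requires strong score-driven loss in sham and none in real, with sham drop-out above the planned 20%. In that scenario nearly all the false rejections favour sham. Participants are to be blinded, so one leaving rule for both arms is the natural base case, and there the type I error is about 5%.

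Nor can the intermediate scores alone take the credit for a standard error near 0.16. With no drop-out at all, an unadjusted comparison has 1.53 × √(2/134) = 0.187, so going below that needs covariate adjustment.

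A two-group test of change is conventional. What remains is that 2.8 does name a method, and that method uses less of the planned data than an available alternative.

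**Conclusion.** The point holds as a modest, cheap improvement and not as a demonstrated bias. The named test is less precise than the planned data allow: SE 0.18 to 0.28 for the decrease, against 0.17 to 0.21 for a baseline-adjusted repeated-measures estimate, with much of the gain due to baseline. It is exposed to bias only if drop-out depends on response and differs by arm. For score-driven loss in sham only, that bias is about -0.16 to -0.23 on the raw score (-0.10 to -0.26 under the wider inputs in step 3) but about +0.01 to +0.05 on the decrease. For a common rule it is at most about 0.06 towards no effect.

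These figures rest on assumed correlations and drop-out rules; the article gives neither, nor drop-out by arm. The small bias on the decrease also relies on drop-out following the level of the score. If participants left because they had not improved since baseline, the cancellation could not be relied on. The model's own near-zero bias holds when drop-out is explained by scores already observed.

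**What to change.** In section 2.8, name as the primary analysis a mixed model for repeated measures of TNSS over weeks 1-8, in all randomised participants as allocated. Include group, week, group-by-week and baseline TNSS, and report the week-8 contrast with its confidence interval. The article fixes no visit for the primary outcome, so the sponsor should confirm that week 8 is the one intended. Keep the two-sample test of the decrease as a sensitivity analysis. Add another that relaxes the missing-at-random assumption, for which the recorded reasons for withdrawal will help.

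Cost: a change of wording in 2.8. The model is available in SPSS and needs no new visits or data. The downside is slightly more modelling work and reliance on missing-at-random, which is why the second sensitivity analysis is needed.

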#### Inclusion criteria

2.2.2

The patient was diagnosed with allergic rhinitis, and the diagnostic criteria refer to the 2008 WHO diagnostic description of allergic rhinitis,^[8]^ aged from 18 to 70 years, had at least 2 years history of typical allergic rhinitis symptoms, and had a positive reaction to any common allergen of allergic rhinitis.

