## Discussion

3

Allergic rhinitis is often induced by weather changes, pollen, animal hair, diet and other allergic factors, the main clinical manifestations are continuous episodes of paroxysmal sneezing, a large number of watery snot, nasal congestion and itching, and some patients have decreased sense of smell, affecting the quality of life.^[22]^ AR is an allergic reaction mediated by IgE under the chemotaxis of various inflammatory cytokines after specific individual contact with antigen. The nasal mucosa produces various pathological changes, and the excitability of the nasal parasympathetic nerve is too strong, resulting in vascular dilation, enhanced permeability, excessive secretion of serous cells,^[23]^ modern medicine is mainly based on drug treatment, Medications include oral and topical histamine H1 receptor antagonists, topical and systemic glucocorticosteroids, chromones, decongestants, topical anticholinergics, antileukotrienes, and oral anti-allergic drugs.^[24]^ However, the adverse reactions caused by it are still a common concern of doctors and patients, and the curative effect is limited, unable to completely relieve the symptoms^[25]^ Therefore, it is necessary to find alternative treatment options for patients with allergic rhinitis.

Ear acupuncture has the characteristics of simple operation, less pain, less side effects and lasting and stable effect. Clinical studies have proved that lung (CO_14_) and wind stream (SF_1,2i_) can relieve congestion and runny nose, adrenal gland (TG_2p_) can resist inflammation and allergy, and its mechanism of action may be to regulate the imbalance of Th1/Th2 cells by inhibiting the differentiation of Th cells to Th2, thereby reducing the synthesis of IgE and inhibiting the occurrence of allergic reactions.^[26]^ Although EAP has been widely used in the treatment of allergic rhinitis in China, there is still a lack of strict clinical studies to verify its curative effect. The existing clinical studies mostly use EAP combined with other treatment schemes, or compare the curative effect with western medicine, and many confounding factors interfere with our evaluation of its curative effect.^[27,28]^ Therefore, we designed this randomized controlled study to determine the efficacy of EAP in the treatment of allergic rhinitis by comparing with sham EAP.

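### The stated primary test ignores baseline score, allergen class and entry date; an adjusted comparison would gain precision at little cost

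*Protocol article*

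**What the plan says.** - **Eligibility (2.2.2).** A patient qualifies who "had a positive reaction to any common allergen of allergic rhinitis". Seasonal and perennial sensitisation are not separated, and no enrolment season is stated.
- **Triggers (3, Discussion).** "Allergic rhinitis is often induced by weather changes, pollen, animal hair, diet and other allergic factors". Some of these vary with the calendar and some do not.
- **Primary outcome (2.5).** "The main outcome indicator is the decrease of Total nasal symptom score". Scores are recorded weekly for 8 weeks of treatment, then every 3 weeks for 12 weeks of follow-up.
- **Randomisation (2.3).** A computer-generated random number table. Stratification by allergen or season is not mentioned.
- **Analysis (2.8).** Measurement data that meet normality and equal variance "are tested by independent sample *T* test, while those inconformable are tested by Mann–Whitney *U* test". On sidedness and level: "the hypothesis test was two-tailed test, and the α level was set to *P* < .05". No covariate is named.
- **Sample size (2.2.1).** Post-treatment scores are the basis: "the real EAP group was 2.82 ± 1.48, and the Sham EAP group was 3.47 ± 1.57", giving 107 per group, or 134 after a 20% allowance for dropout.

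**The concern.** A decrease cannot be computed without a baseline score, and the date of entry is known for everyone. Both may predict the outcome, and the stated tests use neither as a covariate. Subtracting baseline is not the same as adjusting for it: it forces the slope of the follow-up score on baseline to be one, whereas a regression estimates that slope.

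Allergen class and season may add to this. A change score removes a patient's stable level, but not a shift caused by exposure that rises or falls during the weeks of observation. A pollen-sensitised patient who enters as exposure wanes may improve without treatment, while one sensitised to animal hair may not. Left out of the model, that variation is counted as random error. What is at stake is the width of the confidence interval and some power.

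**Working it through.** **Inputs.** Means 2.82 and 3.47 with SDs 1.48 and 1.57, two-sided 5% level, 80% power and 107 per group, from sections 2.2.1 and 2.8. The share of outcome variance explained by covariates, R², is not in the documents and is an assumption throughout.

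**1. The plan's own figure.** The difference is 3.47 − 2.82 = 0.65. The pooled SD is √((1.48² + 1.57²)/2) = 1.526, so d = 0.65/1.526 = 0.426. The normal formula is n = 2(1.960 + 0.842)² × 1.526²/0.65², which gives 87 per group; the exact t-test calculation gives 88. The stated 107 is therefore not reproduced from its own inputs, which is a separate matter. The dropout step does reproduce: 107/0.8 = 133.75, rounded up to 134. With 107 completers per group, t-test power is 87.3%.

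**2. Effect of adjustment.** Covariates that explain a share R² multiply the residual variance by (1 − R²). The standardised difference becomes d/√(1 − R²), and the gain equals a sample larger by the factor 1/(1 − R²). The half-width below is 1.96 × 1.526 × √(1 − R²) × √(2/107).

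| Assumed R² | Sample-size factor | d | 95% CI half-width | Power at 107 per arm |
|---|---|---|---|---|
| 0 | 1.00 | 0.426 | 0.409 | 87.3% |
| 0.05 | 1.05 | 0.437 | 0.398 | 88.9% |
| 0.10 | 1.11 | 0.449 | 0.388 | 90.5% |
| 0.20 | 1.25 | 0.476 | 0.366 | 93.4% |

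These SDs belong to the post-treatment score. No SD is given for the decrease, so the table shows the mechanism and does not forecast the outcome as analysed.

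**3. Baseline adjustment against the change score.** Suppose baseline and follow-up scores have the same SD σ and correlation r. The variance of the decrease is 2(1 − r)σ². The residual variance after regression on baseline is (1 − r²)σ². Their ratio is (1 + r)/2, which is below one for any r below one. The documents do not give r, so the size is open, but the direction is not, apart from the single degree of freedom spent.

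**4. If seasonal variation came on top of the pilot SDs.** The total SD would be √(1.526² + s²). For an assumed seasonal SD s of 0.25, 0.5, 0.75 or 1.0 points, unadjusted power at 107 per arm would be 86.5%, 83.8%, 79.5% or 73.7%. Power would drop just below 80% only at about 0.75 points. Nothing in the documents says that seasonal variation is that large, or that it is missing from the pilot SDs.

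**The case against.** **A two-sample test is a legitimate choice, and covariates are commonly left to the analysis plan.** This is the strongest objection, and part of it stands. Section 2.8 is two sentences of general rule, contradicts nothing, and does not forbid adjustment. But it is not silent either: it names the tests and the rule for choosing between them. That stated choice can be improved, and the point is an improvement and not an error.

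**The seasonal part is unquantified.** This stands in full. The documents give no seasonal variance, no mix of seasonal and perennial patients, and no accrual window. The R² range is assumed and the true value could be near zero.

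**The 20 weeks do not show a mixture of seasons.** Correct. They are each patient's treatment and follow-up, not the recruitment period. With short accrual, a swing common to both arms cancels in the difference, and only allergen-specific variation remains.

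**Main effects of class and period would miss the mechanism.** Correct. A swing confined to pollen-sensitised patients is an interaction of class with period, so the model needs that term.

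**Allergen class may not be on record.** Section 2.2.2 asks only for a positive reaction to some common allergen. It does not show that a full panel is tested or its result kept, and patients positive to both kinds need a category of their own.

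A reader might also infer that the mixture of allergens biases the comparison, or that a chance imbalance invalidates it. The documents do not support that. Randomisation balances season and allergen class on average, and the standard error of the unadjusted test already allows for chance imbalance.

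**Conclusion.** The point holds as one of precision. The stated tests discard information that the trial must have (baseline score, entry date) or may have (allergen class). The benefit of baseline adjustment rests on the algebra above and needs no seasonal assumption. The benefit of the seasonal terms is plausible from the article's own list of triggers, but its size cannot be derived. With an assumed R² of 5% to 20% and the post-treatment SDs, the gain is equivalent to 5% to 25% more patients, or about 2 to 6 percentage points of power at 107 per arm.

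A reader might go further and conclude that the trial is underpowered or the eligibility too broad. Neither follows. On the stated inputs, 107 completers per arm give about 87% against a planned 80%, and the pilot SDs may already contain seasonal variation. The weakness lies in the analysis wording of section 2.8; eligibility and randomisation can stay as they are.

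**What to change.** In section 2.8, replace the unadjusted primary comparison by a linear model (ANCOVA) of the nasal symptom score with arm and baseline score. Using the follow-up score or the decrease as response gives the same treatment estimate once baseline is in the model. The t test or Mann–Whitney U test can remain as a sensitivity analysis.

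Add calendar period of entry and, where the eligibility test result is recorded, allergen class in three categories (seasonal, perennial, both), with their interaction. Fix the classification rule and the period boundaries before unblinding.

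**Cost.** Baseline adjustment takes one degree of freedom and no new data. For the rest, keep the periods coarse. With two periods and three classes, for example, the extra terms use 1 + 2 + 2 = 5 degrees of freedom. With baseline that makes 6, out of 2 × 107 − 2 = 212. If all six explained nothing, the variance of the treatment estimate would rise by roughly 6/(214 − 6 − 3) = 2.9%. The power figures above leave out this small charge. Recording allergen class may need one extra field on the case report form. No patient, visit or eligibility rule changes.
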